### Sample size calculation

The primary endpoint is a difference in HLA-DR expression on monocytes exactly quantified by analysing antibody-binding molecules/cell within the first week (day 3–4) post-trauma. Numbers of patients to be enrolled were calculated on the basis of a pilot study (n = 26) [6]. The sample size calculation was performed for an effect size of 0.18. The type one error was be set to 0.05 (two-sided); type two error was set to 0.2. The number of patients eligible for evaluation (for testing the hypothesis by the one way anova) is 56 in total (software nquery, version 7.0). Due to an expected rate of drop-outs/missing data of 50% and non-parametric testing, where applicable, the number of patients to be recruited increases to 118 in total. The expected rate of drop-outs/missing data relates to the structural conditions of acute SCI care in terms of i) delayed transfer to specialized SCI trial centers after primary care in external non-specialized centers and ii) loss to follow up due to discharge from inpatient rehabilitation, particularly in the control group or in cases of mild incomplete SCI. Consequently, to allow for a completion of the study within a feasible time period consideration of missing values is unavoidable.

The sample size calculation was performed taking the asymmetric natural distribution of the neurological lesion level into account [20]. Injury to the cervical and high thoracic spinal cord has the highest incidence and represents the largest group of SCI patients. Thus, the relation of the 3 groups to each other was determined as follows based on the pilot trial data i) 41% (n = 48); ii) 26% (n = 31); iii) 33% (n = 39).

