### Statistical analysis

Data analysis of the primary endpoint consists of a comparison, between the 3 groups at the early and subsequent follow-up assessment points using one-way ANOVA or nonparametric tests, if appropriate. The analysis will be performed using the full dataset comprising all patients included according to the criteria as defined in the study protocol. In addition, in patients with complete intra-individual datasets also changes over time within the groups will be assessed with descriptive methods. Furthermore, in the case of a relevant amount of missing values, multiple imputation will be taken into consideration for verification of the analysis of the original data. Data obtained from patients treated with methylprednisolone will be primarily analyzed in a casuistic manner.

The statistical analysis of the administrative interim evaluation has been performed using SPSS for Macintosh, Version 19.0.

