### Observation period

Observational time points (Figure 2) range from acute to sub-acute stages after SCI comparable to the pilot study [6]. Here, the time schedule corresponded to the hallmarks of parenchymal inflammation following SCI. The implementation of sub-acute assessments is in line with previous trials that demonstrated mid- and long-term alterations of the immune system after SCI [8,18,19].

The setting of defined time corridors instead of time points provides a more complete tracking of the participants. In order to prevent a high amount of missing datasets due to loss to follow-up, the protocol allows an inclusion at each documentation time point.

The administrative interim analysis of data completeness for the main laboratory parameters indicates - depending on the group or visit – a completeness of data between 24% and 91% with critical rates of completeness at visit 1 and visit 5, particularly in the control group (Table 5). As a consequence, the recruiting centers have been requested to enroll the patients as soon as possible after injury. Additionally, we intend to address the challenge of loss to follow up by travelling to external rehabilitation centers or by phone calls to remind patients of their study visit at the outpatient clinic. The rate of complete longitudinal datasets ranges between 18% and 36% but is expected to increase during the further trial course since trial routines are better established. Noteworthy, the sample size calculation takes 50% of missing values into account and was performed for one-way ANOVA. Repeated measure analysis requires lower sample sizes. Therefore, it seems feasible that a relevant amount of complete longitudinal datasets can be achieved also for the description of the intra-individual course of the SCI-IDS. Pursuing this study concept, serial investigations on short- and mid-term changes of the immunological function are provided.

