### Possible consequences

The objective of this study is the longitudinal characterization of immunological markers of the innate and acquired immune system after traumatic SCI. Furthermore, the aim is to detect diagnostic surrogate parameters for the clinical application after SCI. The characterization of a causative relationship between the lesion level and/or SCI severity and the type and/or extent of the immune response after SCI - including a critical characterization of the methylprednisolone effect - is essential for the implementation of therapeutic studies. Understanding and recognition of the immunological dysfunction and the altered susceptibility to infections may then assist in consecutive decision-making. This is relevant for the stratification of patients who are at high or low risk for infectious complications [33]. In addition, these findings may also hold the key for early therapeutic immunomodulation aiming to improve overall survival by anticipation and prevention of life-threatening infectious complications.

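### The within-patient time course is restricted to complete datasets (18–36% at interim, at most 4 of 17 controls), so its group curves describe small, differently selected subsets

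*Protocol article*

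**What the plan says.** All places are in the protocol article.

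- **Statistical analysis.** The main analysis compares the three groups at the early and later visits by one-way ANOVA or a nonparametric test, using the full dataset. As an addition, "in patients with complete intra-individual datasets also changes over time within the groups will be assessed with descriptive methods". Multiple imputation is only to be considered if much is missing, as a check on the analysis of the observed data.
- **Observation period (Discussion).** "The rate of complete longitudinal datasets ranges between 18% and 36% but is expected to increase during the further trial course". The section argues that "Repeated measure analysis requires lower sample sizes", and concludes that it seems feasible that "a relevant amount of complete longitudinal datasets can be achieved also for the description of the intra-individual course of the SCI-IDS". It also describes earlier enrolment, travel to outside rehabilitation centres and telephone reminders.
- **Possible consequences.** "The objective of this study is the longitudinal characterization of immunological markers of the innate and acquired immune system after traumatic SCI".
- **Sample size calculation.** Missing data are put down to delayed transfer and to "loss to follow up due to discharge from inpatient rehabilitation, particularly in the control group or in cases of mild incomplete SCI".
- **Assessment time points.** There are five visits. The first falls within 31 hours of injury; patients may also join later, and extended windows are offered for visits 2 to 5 only.

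**The concern.** Several of the trial's questions are about course: whether lymphopenia is transient, whether functional deficits outlast the acute phase, and how the immune depression develops within a patient. The ANOVA at each visit compares groups but does not estimate change within patients. The only analysis that does so admits patients with complete datasets alone.

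To qualify, a patient must have been sampled within 31 hours and still be reached at 10 weeks. By the article's own account, those who fail are not a random subset: they are late transfers, controls and patients with mild incomplete lesions. Each group's curve would then rest on a minority, and the selection differs by group. A difference in course between groups could partly reflect who could be sampled at both ends. Patients with two, three or four results contribute nothing to the time course.

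**Working it through.** **Inputs** (Tables 4 and 5; flow-cytometry results in the per-protocol population)

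| Group | Interim n | Visits 1 to 5 | Results | Planned n |
|---|---|---|---|---|
| SCI T4 and above | 28 | 17, 20, 22, 22, 16 | 97 | 48 |
| SCI T5 and below | 11 | 6, 6, 8, 10, 5 | 35 | 31 |
| Control | 17 | 9, 12, 14, 12, 4 | 51 | 39 |
| Overall | 56 | 32, 38, 44, 44, 25 | 183 | 118 |

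Of 56 × 5 = 280 possible results, 183 exist (65%).

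**1. The stated 18–36%.** The article gives no per-patient cross-tabulation, so the rate cannot be rebuilt exactly, but whole-number counts fit it. The low end matches 3/17 (17.6%), 2/11 (18.2%) or 5/28 (17.9%). The high end matches 10/28 (35.7%) or 4/11 (36.4%). It therefore looks like a range across the three groups.

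**2. Cap on controls.** Complete patients cannot outnumber those seen at the sparsest visit. For controls that is visit 5: 4/17 = 23.5%. With the stated floor of 18%, controls have 3 or 4 complete datasets.

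**3. Controls at full enrolment, interim rates held.** 39 × 3/17 = 6.9 and 39 × 4/17 = 9.2. Allowing for the interim drop-out of 4/60 (factor 56/60) gives 6.4 and 8.6. So about 6–9.

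**4. Complete patients overall, if 18–36% is the range across groups.** One group must sit at 18% and one at 36%, and the rest lie between.
- Fewest: 5 (T4 and above) + 4 (T5 and below) + 3 (control) = 12.
- Most: 10 + 4 + 3 = 17. With 4 controls, the 18% group has to be one of the SCI groups, and the most is 10 + 2 + 4 = 16.

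**5. Results unused for the time course.** Share unused = 1 − 5 × complete patients / results.
- Overall: 1 − 60/183 = 67%; 1 − 85/183 = 54%.
- Controls: 1 − 15/51 = 71%; 1 − 20/51 = 61%.

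**6. Selection by group.** Visit 5 is present in 16/28 = 57% of T4 and above, 5/11 = 45% of T5 and below, and 4/17 = 24% of controls. Visit 1 is present in 61%, 55% and 53%.

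**7. The repeated-measures remark.** For a between-group test on a five-visit mean with common within-patient correlation r, the 56 evaluable patients become 56 × (1 + 4r)/5. With r assumed, since the article gives none: r = 0.5 gives 34, r = 0.7 gives 43 and r = 0.9 gives 52. All are below 56 and use complete patients only.

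**The case against.** The strongest reply is that this is a supplementary description. The main comparisons use the full dataset at every visit, so all 183 interim results are analysed. That stands. A reader might infer that the samples are thrown away, or that the complete-dataset description is the only route to the longitudinal objective. Neither is supported: the loss is confined to the within-patient analysis, and the visit-by-visit comparisons serve the objective in part.

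Other replies also have force:

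- **The rate may improve.** The article expects it to, and plans earlier enrolment, travel and reminders. So 6–9 controls is a projection at interim rates. A reader might also infer that only long-stay patients can be complete; the planned travel and reminders mean that discharged patients can be too.
- **The repeated-measures remark is right in general.** A reader might infer that such an analysis saves patients only by using partial records. Step 7 shows otherwise. The difficulty is narrower: the Statistical analysis section plans no repeated-measures model, so the remark cannot support a rule that admits only complete datasets to a description.
- **Bias is not demonstrated.** The article links missingness to transfer, discharge, group and severity, not to early HLA-DR values. An illustrative simulation errs upward or downward according to whether low or high early values are assumed to favour retention. A reader should infer no direction or size.
- **Multiple imputation is mentioned.** It is conditional, and is described only as verification, so it does not replace the rule.

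Modelling detail is often left to an analysis plan, but here the article states the rule itself, so the rule can be judged.

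**Conclusion.** The concern holds as a weakness in a stated method that should be changed. The primary group comparison and the sample size are unaffected.

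At interim, 3–4 of 17 controls and 12–17 of 56 patients overall would inform the time course, leaving about 54–67% of results unused for that purpose. A reader applying 36% to all 56 patients would get 20 complete datasets and 45% unused. That is not attainable under the across-groups reading: even with 4 controls and 5 patients at T5 and below (their visit 5 counts), 11 of 28 (39%) at T4 and above would be needed, over the stated ceiling.

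These figures assume that complete means all five visits, which the article implies but does not spell out; that 18–36% is a range across groups; and, for the projection of 6–9 controls, that interim rates persist. That the groups are differently selected follows from the article's own account of missing data and from Table 5. Whether and how far this distorts the curves is unknown.

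**What to change.** Describe the time course with a linear mixed model containing group, visit and group-by-visit interaction, with HLA-DR on a suitable scale, fitted to every patient with at least one sample. Report within-group changes and between-group differences in change with 95% confidence intervals. Keep the complete-dataset plot as a sensitivity display, with the number of patients per group shown.

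The general remark about repeated-measures sample sizes in the Observation period section can stay, but should not be used to justify the complete-dataset rule.

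The cost is one paragraph of analysis text and some additional modelling, with no new patients or samples. The model relies on data being missing at random given what was observed. That support is weakened because visit 1 is absent in 24/56 = 43% of patients (8/17 = 47% of controls), so the early value is often unavailable. This should be stated with the results.

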## Discussion

The SCIentinel trial aims to define SCI-IDS characteristics. We investigate the hypothesis that SCI-IDS is not restricted to quantitative immune suppression (cell depletion) [5-8], but also affects qualitative immune function of 'spared’ immune cells. Qualitative dysfunction of immune cells translates into suppressed innate and adaptive immune cell function that finally leads to impaired host defense [29]. Qualitative effects may extend into chronic SCI [29] and therefore the identification of patients prone to develop infections is also relevant during long-term follow up. Moreover, according to the proposed 'neurogenic’ origin of the SCI-IDS we suggest rostral and complete spinal cord lesions to be associated with a more severe immune depression syndrome compared to more caudal or incomplete lesions. Furthermore we intend to investigate a putative sustained extension into chronic disease phases after SCI. Together, this is embedded the longitudinal prospective trial design and in a power calculation that takes differences between rostral and caudal neurological levels into account. In addition, the impact of facultative co-treatment with high dose methylprednisolone, which may further aggravate SCI-IDS is accessible for descriptive analysis.

### Spine trauma

In order to differentiate the SCI-related 'neurogenic’ effect on the immune system from the 'non-neurogenic’ effect of the surgical intervention/trauma itself (activation of the stress axis/post-aggression syndrome) the study protocol incorporates a control group of patients with isolated vertebral fracture without neurological deficit. Of note, this refinement of the control group definition by the SCIentinel trial overcomes a weakness of the pilot study where patients after smaller surgical interventions such as arthroscopy served as control group [6], which only insufficiently mimics the post-aggression syndrome caused by surgical stabilization of the spine.

In order to evaluate the impact of the lesion height we assess differences between rostral and caudal spinal cord lesions. Consequently, SCI patients were divided into two groups with/without expected impairment of the major sympathetic outflow and compared with the controls applying a three-group strategy for analysis (Figure 1). To assess the effect of lesion severity, we compare complete (AIS A) with incomplete lesions (AIS B-D) in a descriptive sub-group analysis.

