## Abstract

**Background:**

Infections are the leading cause of death in the acute phase following spinal cord injury and qualify as independent risk factor for poor neurological outcome (“disease modifying factor”). The enhanced susceptibility for infections is not stringently explained by the increased risk of aspiration in tetraplegic patients, neurogenic bladder dysfunction, or by high-dose methylprednisolone treatment. Experimental and clinical pilot data suggest that spinal cord injury disrupts the balanced interplay between the central nervous system and the immune system. The primary hypothesis is that the **S**pinal **C**ord **I**njury-induced **I**mmune **D**epression **S**yndrome (SCI-IDS) is 'neurogenic’ including deactivation of adaptive and innate immunity with decreased HLA-DR expression on monocytes as a key surrogate parameter. Secondary hypotheses are that the Immune Depression Syndrome is i) injury level- and ii) severity-dependent, iii) triggers transient lymphopenia, and iv) causes qualitative functional leukocyte deficits, which may endure the post-acute phase after spinal cord injury.

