**Discussion:**

The objectives are to characterize the dysfunction of the innate and adaptive immune system after spinal cord injury and to explore its proposed 'neurogenic’ origin by analyzing its correlation with lesion height and severity. The trial protocol considers difficulties of enrolment in an acute setting, and loss to follow up. The administrative interim analysis confirmed the feasibility of the protocol. Better understanding of the SCI-IDS is crucial to reduce co-morbidities and thereby to attenuate the impact of disease modifying factors to protect neurological “outcome at risk”. This putatively results in improved spinal cord injury medical care.

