### Neurological classification

The neurological evaluation is performed according to the International Standards for Neurological Classification of Spinal Cord Injury (ISNCSCI), a revision of ASIA classification [23,24]. Within the ISNCSCI-regime the ASIA impairment scale (AIS) as a measure for completeness of the injury, and the single neurological level of the lesion are assessed.

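### Level and severity dependence are both hypotheses, but no analysis described in the protocol contains both variables

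*Protocol article*

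**What the plan says.** The Abstract (Background) puts the two dependencies side by side: "Secondary hypotheses are that the Immune Depression Syndrome is i) injury level- and ii) severity-dependent". The Abstract (Discussion) says the proposed neurogenic origin will be explored "by analyzing its correlation with lesion height and severity". The opening of the main Discussion gives the expected direction for both: "we suggest rostral and complete spinal cord lesions to be associated with a more severe immune depression syndrome compared to more caudal or incomplete lesions".

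The analyses described are these:

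- **Level.** The Statistical analysis section compares the three groups (SCI at T4 or above, SCI at T5 or below, vertebral fracture control) "using one-way ANOVA or nonparametric tests, if appropriate". It mentions no severity term.
- **Severity.** The Spine trauma section of the Discussion says "we compare complete (AIS A) with incomplete lesions (AIS B-D) in a descriptive sub-group analysis". It does not say whether this is done across all SCI patients, within level groups or with adjustment for level.

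Both variables are available. Under Neurological classification, "the ASIA impairment scale (AIS) as a measure for completeness of the injury, and the single neurological level of the lesion are assessed". Under Possible consequences the authors go further: "The characterization of a causative relationship between the lesion level and/or SCI severity" and the immune response is called essential for later therapeutic studies.

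**The concern.** The protocol expects two characteristics of the same patients to lower the same outcome, and describes a separate analysis for each. A one-way ANOVA has one factor, and here that factor is the level group, so AIS grade plays no part in it. The AIS comparison is a separate description with no stated link to level.

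Nothing balances AIS grade across level groups, because patients are not randomised to them. Loss of data could add imbalance. The Sample size calculation section expects loss to follow-up particularly in controls and in mild incomplete SCI, so missingness is expected to depend on severity. Table 5 shows visit 2 flow cytometry complete in 20 of 28 patients (71%) at T4 or above but 6 of 11 (55%) at T5 or below, so it may depend on level too. AIS shares that were equal at enrolment need not be equal among the patients analysed.

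At stake is interpretation. A rostral-caudal difference could partly reflect a different share of complete lesions, and an AIS A versus B-D difference could partly reflect level.

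**Working it through.** **1. The plan's own sample size, to fix the number of evaluable SCI patients.** From the Sample size calculation section: effect size ("The sample size calculation was performed for an effect size of 0.18"), two-sided alpha 0.05, power 0.80, 56 evaluable, 118 recruited as 48 / 31 / 39.

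- Read 0.18 as the variance of the means over the error variance (f²). Three-group noncentral F, noncentrality = N × 0.18: power is 79.5% at N = 56 and 80.3% at N = 57. The stated 56 is reproduced to within one patient. Other readings do not fit: f = 0.18 needs N = 301, and eta² = 0.18 needs N = 48.
- 56 / (1 − 0.5) = 112. An assumed allowance of about 5% for nonparametric testing gives 112 × 1.05 = 117.6, i.e. 118.
- Evaluable SCI patients: 56 × 48/118 = 22.8 and 56 × 31/118 = 14.7, so about 23 + 15 = 38.

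**2. Shift in a crude severity comparison.** The AIS shares and the level effect are assumptions. Suppose there is no severity effect and HLA-DR is lower by L SD in high lesions. The spurious AIS A minus B-D difference is then

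−L × [share of high lesions among AIS A − share of high lesions among AIS B-D].

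With AIS A in 40% of the 48 high and 60% of the 31 low lesions:

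- AIS A: 0.40 × 48 = 19.2 high and 0.60 × 31 = 18.6 low; share high = 19.2 / 37.8 = 0.508.
- AIS B-D: 28.8 high and 12.4 low; share high = 28.8 / 41.2 = 0.699.
- Difference in shares = −0.191. For L = 0.5 to 1.0 the shift is 0.10 to 0.19 SD, making AIS A look better than it is and so masking part of any severity effect.

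Other assumed shares, with L = 1 SD:

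| AIS A share, high / low | Size of shift | Direction |
|---|---|---|
| 50% / 50% | 0 | none |
| 40% / 50% | 0.10 SD | masks severity |
| 40% / 60% | 0.19 SD | masks severity |
| 35% / 65% | 0.29 SD | masks severity |
| 60% / 40% | 0.19 SD | exaggerates severity |

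**3. The same mechanism in the level comparison.** With a severity effect of 0.5 to 1.0 SD and AIS A shares 20 percentage points apart, the rostral-caudal contrast shifts by 0.20 × 0.5 to 0.20 × 1.0 = 0.10 to 0.20 SD.

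**4. Precision.** With 38 SCI patients split 19 / 19 by AIS, the 95% half-width is t(0.975, 36) × √(2/19) = 2.03 × 0.324 = 0.66 SD. The difference detectable with 80% power is 0.93 to 1.03 SD for AIS A shares of 30% to 60%.

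**5. Cost of adjusting.** Variance inflation is 1 / (1 − φ²), where φ is the correlation between level group and AIS. For 40% / 60%, φ = −0.195 and inflation is 1.04. Across the scenarios checked it is at most about 1.10, which widens the interval by no more than √1.10 = 1.05, or about 5%.

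**The case against.** Four points on the other side deserve weight.

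- **The article does not call the AIS comparison pooled or unadjusted.** A reader might infer that from the one sentence in the Discussion, but the text is silent, and detail on a secondary description may sit in the full protocol or analysis plan. This stands. What the article does name is a one-factor test for level and a separate description for severity, and neither is said to include the other variable.
- **A reader might conclude that the trial cannot separate level from severity.** The document does not support that. Both variables are recorded, and step 5 shows that a joint model could separate them at little cost in variance.
- **A descriptive analysis of an unpowered secondary hypothesis is proportionate.** This stands: the descriptive label is not an error. The causal wording under Possible consequences is an ambition and not an analysis specification, though two unlinked comparisons would be weak support for it.
- **The shift is small and rests on assumptions.** It is 15% to 29% of the 0.66 SD half-width (0.10 / 0.66 and 0.19 / 0.66). To say that it would hide a severity effect goes too far; imprecision is the larger limit, and adjustment does not cure that.

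A model with main effects only also assumes the same severity effect at both levels. The Figure 2 legend expects sympathetic outflow to be partly or wholly preserved in low lesions, so completeness might matter more in high ones. That is a reason to show the AIS comparison by level group as well.

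**Conclusion.** The point holds in a limited form. Level and severity dependence are both stated hypotheses, both are expected to worsen immune depression, and no analysis described in the article contains both variables. In observational groups, any difference in AIS share between level groups would mix the two effects.

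The size is unknown from the document. Under the main illustrative assumptions it is 0.10 to 0.19 SD in a crude severity difference and 0.10 to 0.20 SD in the rostral-caudal contrast. It is zero if AIS shares are equal, and its direction cannot be known in advance. This is a gap in the described analysis that the collected data can close; it is not a flaw in the design. Severity conclusions should be treated as exploratory in either case.

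**What to change.** In SCI patients, add one secondary, exploratory model of monocytic HLA-DR at the primary time point, on the same scale as the primary analysis. Include level group (T4 or above / T5 or below) and AIS (A / B-D) together, and report both adjusted estimates with 95% CI. Keep the descriptive AIS comparison, but tabulate it by level group so that a severity effect that differs between levels can be seen. Label conclusions on severity exploratory and word any causal statement accordingly.

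The cost is one degree of freedom, with no extra patients or measurements. The severity interval will be wide, about ±0.66 SD with about 38 evaluable SCI patients split evenly and slightly more after adjustment. Estimates within level groups will be less precise still, with about 23 and 15 patients.
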